### Randomization procedure

The randomization list will be computer-generated by a statistician from the Clinical Research Unit of Paris-Est Créteil University, independent from the study. The randomization number for each participant will be requested by the evaluating investigator (blinded) at the end of Visit 2 (M6) and then transmitted electronically to the referring coordinator (unblinded) of the center. Each participant will be randomized into one of the two treatment groups: the CONV group (Conventional Therapy) and the GSC group (Guided Self-rehabilitation Contract). Randomization will be stratified by center.

### Study population

To participate in this study, subjects must have the decision making capacity to give informed written consent based on the investigator’s judgment, and meet all of the inclusion criteria and none of the exclusion criteria listed below.

#### Inclusion criteria

Hemiparesis due to stroke, for over a year before enrolment;Age > 18 years;Ability to ambulate over 10 m independently, barefoot and without technical aid;Maximal 10-m ambulation speed between 0.1 and 1.3 m/sec;Modified Frenchay Scale score > 2/10 and < 8/10;Written consent to participate in the protocol, signed by the patient

#### Exclusion criteria

Recurrent stroke;Significant orthopedic disorder in lower limb;Cognitive, phasic or behavioral dysfunction affecting patient participation;Non affiliation to medical insurance system.

### Statistical methods

#### Sample size

With respect to the Modified Frenchay Scale, based on an average score of 4.4 ± 1.9 in a similar population, [82] the alternative hypothesis (H1) is an improvement of 30% in the GSC group versus a 10% improvement in the CONV group. To demonstrate this hypothesis with a bilateral 80% power and an alpha score of 5%, *n* = 62 subjects per group are required for a total of 124 participants.

With respect to the maximal ambulation speed over 10 m, with an assumed baseline ambulation speed of 0.63 ± 0.43 m/sec and with the hypothesis of a 50% improvement in the GSC group versus a 10% improvement in the CONV group, at least *n* = 47 participants per group are required using a bilateral power of 80% with an alpha of 5% [47]. A total of 124 patients will thus be included in the protocol. This number should also allow sufficient power to evaluate secondary criteria, including a description of the monthly frequencies of the rehabilitation sessions, of the required aids and allowances and therefore an estimation of the cost from the point of view of the health insurance and the State.

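### The Modified Frenchay Scale inputs require about 75 per group, not 62; at 62 per group they give about 73% power, not the stated 80%

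*Protocol article*

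**What the plan says.** The Sample size section treats the two co-primary endpoints separately.

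- **MFS.** The calculation is "based on an average score of 4.4 ± 1.9 in a similar population" and assumes "an improvement of 30% in the GSC group versus a 10% improvement in the CONV group". It is made "with a bilateral 80% power and an alpha score of 5" per cent. The result is "62 subjects per group are required for a total of 124 participants".
- **Walking speed.** The inputs are "an assumed baseline ambulation speed of 0.63 ± 0.43 m/sec" and the "hypothesis of a 50% improvement in the GSC group versus a 10% improvement in the CONV group", again two-sided at 5% with 80% power. The result is at least 47 per group.

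The larger figure is carried forward: "A total of 124 patients will thus be included in the protocol". The section gives no SD of change, no correlation between visits, no covariate adjustment and no allowance for loss.

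Elsewhere, Procedures places consent at D1, Randomization procedure places allocation at the end of the M6 visit, and Statistical analysis puts the main comparison between M6 and M18. Procedures also ends participation on a diagnosis of recurrent stroke. Analysis of the randomized study plans mixed models for the criteria and their M6–M18 changes.

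**The concern.** All the inputs of a two-group comparison of means are printed, so the result can be checked directly, and 62 is too small by 12 or 13 per group. This is the calculation that sizes the trial, since walking speed alone would need only 47 per group. If the figure is wrong, the trial claims 80% power for its upper-limb co-primary endpoint when its own assumptions do not deliver it. On those assumptions the chance of missing a true MFS effect is about 27% instead of 20%, and anyone reading a null MFS result against the stated 80% would take it as stronger evidence than it is.

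**Working it through.** **Inputs (all from the Sample size section).** MFS mean 4.4, SD 1.9; improvements of 30% and 10%; two-sided α = 0.05; power 80%; equal groups. Walking speed mean 0.63, SD 0.43 m/s; improvements of 50% and 10%; same α and power.

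**Formulas.** Normal approximation: n per group = 2(1.960 + 0.842)² / d², where d = difference / SD. The t-test version uses the noncentral t distribution with 2n − 2 degrees of freedom and noncentrality d√(n/2).

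**Step 1: reproduce the walking-speed figure.**
- Difference = 0.63 × (0.50 − 0.10) = 0.252 m/s; d = 0.252 / 0.43 = 0.586.
- Normal formula: 45.7, so 46. Two-sided t-test: 46.7, so **47**, exactly as stated.

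A plain two-sided t-test on the baseline SD therefore accounts for the article's second calculation.

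**Step 2: the same method on the MFS.**
- Difference = 4.4 × (0.30 − 0.10) = 0.88; d = 0.88 / 1.9 = 0.463.
- Normal formula: 73.2, so 74. Two-sided t-test: 74.15, so **75**. Stated: 62.

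**Step 3: power at 62 per group.**
- Noncentrality = 0.463 × √31 = 2.58. Normal approximation: Φ(2.58 − 1.96) = 73.2%. t-test: **72.5%**.
- Walking speed at 62 per group: 89.9%.

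**Step 4: can another reading give 62?**

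| Variant for the MFS | n per group |
|---|---|
| One-sided 5% | 58 (normal), 59 (t-test) |
| Difference rounded up to 0.9 | 70 to 71 |
| Two-sided, inflated for a Wilcoxon test | 78 |
| Two-sided α = 0.025 | 89 to 90 |
| One-sided plus 5% dropout | 62 to 63 |
| One-sided plus Wilcoxon inflation | 61 to 62 |

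Only the last two come close. Both contradict the stated two-sided test and need an additional factor that is not stated. With a two-sided test, 62 would need an SD of about 1.75 or a difference of about 0.96 (normal formula), or a gain from using the M6 score.

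**Step 5: what the M6 score could contribute.** Let r be the M6–M18 correlation, an assumption because the article gives none, and let the SD be 1.9 at both visits.
- Baseline-adjusted analysis, variance factor 1 − r²: 73.2(1 − r²) ≤ 62 gives r ≥ 0.39; by t-test, about 0.41. Power at 62 is 79.7% at r = 0.40, 80.5% at r = 0.42 and 89% at r = 0.6.
- Simple change score, variance factor 2(1 − r): 73.2 × 2(1 − r) ≤ 62 gives r ≥ 0.58. Power at 62 is 65% at r = 0.4, 72.5% at r = 0.5 and 82% at r = 0.6.

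**Step 6: loss between D1 and M18.** The rates are illustrative, since none is given.
- 10% loss: 62 × 0.90 ≈ 56 per group; unadjusted power 68%.
- 20% loss: 62 × 0.80 ≈ 50 per group; unadjusted power 63%.

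**The case against.** The strongest reply is that 73% is the power of an unadjusted comparison, whereas the article plans mixed models on M6–M18 change. Depending on the correlation, the planned analysis could have less than 80% power (a change score with r below about 0.58) or well over it (baseline adjustment with r of 0.5 or more). That is right, and it means 73% should not be presented as the power the trial will certainly have. It does not make 62 follow from the printed inputs: no correlation or SD of change is stated, and the walking-speed figure is reproduced without one.

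A related point is that matching 47 does not prove the MFS figure was meant to use the same method, since the two calculations cite different sources. An SD or correlation may have been dropped from the article. This also stands: the cause of the discrepancy is unknown, but the discrepancy is there. The MFS entry limits (above 2 and below 8) might likewise give a smaller SD than 1.9, but the article describes the source population as similar and uses 1.9.

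Finally, a journal article may leave an attrition allowance to the full protocol, and the 10% and 20% rates are only scenarios. Loss is therefore secondary. What can be said is that the article equates the number required with the number included at D1. The arithmetic error stands without it.

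**Conclusion.** The stated MFS sample size is wrong on its own terms. The printed inputs need 75 per group by t-test (74 by the normal formula), 148 to 150 in total, against 62 and 124. At 62 per group they give 72.5% power, a type II error of about 27% instead of 20%. Neither rounding nor a one-sided test accounts for the gap.

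The 72.5% assumes that 1.9 is the SD of the quantity compared, that the comparison is unadjusted and that nobody is lost. Loss would lower it; adjustment for the M6 score would raise it by an amount that depends on a correlation the article does not give. Walking speed is unaffected, with about 90% power at 62 per group.

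**What to change.** If 62 came from an SD of change or a correlation that was left out, print that value and its source. Otherwise:

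1. Replace the MFS statement with wording such as: *With 62 analysed per group, an SD of 1.9 and a difference of 0.88 points, the unadjusted comparison has 73% power at two-sided 5%; 80% would need 75 per group.*
2. State that the MFS analysis adjusts for the M6 score, and that this gives 80% power at 62 per group if the M6–M18 correlation is at least about 0.42. Give the power over a range of correlations. An unadjusted change score should not be relied on, because it needs about 0.58.
3. Give the power for 10% and 20% loss counted from D1, labelled as scenarios.

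The cost is wording only. The M6 score is already collected and no enrolment is added. The stated power becomes less favourable unless the adjusted analysis is adopted.

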## Objectives

The primary objective of this study is to evaluate changes in lower limb and upper limb motor function after 1 year of Guided Self-rehabilitation Contract compared to conventional therapy alone, at a chronic stage following stroke.

The secondary objectives include the evaluation of: i) quality of life at the end of 1 year with each of the two treatment modalities; ii) direct socioeconomic costs of the two physical treatments from the point of view of the health coverage system; iii) persistence of lower limb and upper limb motor function changes 6 months after the end of the one-year experimental study period; iv) amount of self-rehabilitation in the experimental group over 12 months; v) current, real-life amounts of conventional rehabilitation provided for chronic hemiparesis in the French health system. vi) psychological and occupational therapy endpoints with the two treatments, for a sub-group of 44 patients.

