### Outcome measures

To evaluate motor function beyond 1 year after stroke, the two co-primary outcome measures are as follows:For the lower limb: capacity of ambulation, assessed by the maximal ambulation speed barefoot without technical aids over 10 m, starting and ending in a seated position (re-assessed by a blinded investigator based on video recordings) [61]. This parameter is correlated with most of the kinematic parameters of gait in hemiparesis and characterized by high intra- and inter-rater reliability [61–64]. Finally, ambulation tests over 10 m (AT10) have strong ecological validity, with respect to the use of walking in natural environments [65–67].For the upper limb: the Modified Frenchay Scale (MFS) [68, 69]. This scale is a modification of the Frenchay Arm Test, that consisted in a binary pass-fail rating of seven unimanual activities of daily life [4]. The MFS consists of video-recording ten activities of daily life (4 uni-manual activities using the paretic hand and 6 bimanual activities, in which the paretic hand assists the other hand) and rating them on a ten-point visual analog scale based on the video-review. The maximal score for each task is 10 and the total score is the mean of the ten scores. The rating of each task of the Modified Frenchay Scale demonstrated excellent intra- and inter-reliability and MFS has also been validated against a well-known subjective scale of perceived function (Disability Assessment Scale, DAS) [70, 71]. The study will use a central, a single blind investigator for MFS rating of all visits for all study participants.

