#### Analysis of the randomized study

The analysis of the randomized study will be carried out based on intent to treat and per protocol.

The primary and secondary criteria and their changes from M6 to M18 will be compared between the two groups using mixed models. The changes will also be compared at M24, i.e. 6 months following the end of the study treatment. These same analyzes will be carried out by subgroups, comparing the availability of a psychological follow-up or not, ie in the participants recruited by the Mondor-Lariboisière centers versus those of the other centers.

A multivariable analysis will be carried out by considering the characteristics of the patients (age, sex), the center, the initial severity parameters of the disease (sensory disturbances) or time since stroke, as well as the availability or not of a psychologist.

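### Two co-primary endpoints are each sized at two-sided 5% and 80% power with no rule linking them, so the design meets 5%/80% neither if one success is enough nor, on its own figures, if both are needed

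*Protocol article*

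**What the plan says.** Under Outcome measures, the protocol article introduces its primary endpoints with "the two co-primary outcome measures are as follows": maximal barefoot speed over 10 m for the lower limb and the MFS for the upper limb. The Objectives section has one primary objective covering both limbs, to "evaluate changes in lower limb and upper limb motor function after 1 year of Guided Self-rehabilitation Contract compared to conventional therapy alone".

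The Sample size section makes two separate calculations.

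- **MFS:** "based on an average score of 4.4 ± 1.9 in a similar population" and "an improvement of 30% in the GSC group versus a 10% improvement in the CONV group", "with a bilateral 80% power and an alpha score of 5"%, giving 62 per group.
- **Speed:** "with an assumed baseline ambulation speed of 0.63 ± 0.43 m/sec", with a 50% gain under the Guided Self-rehabilitation Contract (GSC) against 10% under conventional therapy (CONV), giving 47 per group. The text reads "participants per group are required using a bilateral power of 80% with an alpha of 5"%.

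The larger figure sets the total of 124. On analysis sets, the article says: "The analysis of the randomized study will be carried out based on intent to treat and per protocol". Neither set is named as primary, there or under Research design. No section gives a success rule, an alpha split, a testing order or a joint power.

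**The concern.** Two endpoints that share primary status need a rule that connects them, and the sample size has to match that rule.

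- If a positive result on either endpoint counts as success, testing each at 5% does not hold the trial at 5%.
- If both must be positive, the error rate is safe, but the chance of winning both is lower than the chance of winning either one. 80% on each alone is then not 80% for the trial.

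Taking the larger of two stand-alone sample sizes answers neither case. At stake is whether a result on one limb only, an outcome that the protocol's own figures make quite possible, can be presented as confirmatory. That choice is credible only if it is made before unblinded results are seen.

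**Working it through.** **Inputs from the Sample size section.** MFS: difference (0.30 − 0.10) × 4.4 = 0.88, SD 1.9, standardised 0.463. Speed: difference (0.50 − 0.10) × 0.63 = 0.252 m/s, SD 0.43, standardised 0.586. "Bilateral" is read as two-sided. **Assumed:** correlation r between the two test statistics of 0 to 0.5; the article gives none.

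**Step 1: reproduce the stated sizes.** n per group = 2 × (1.960 + 0.842)² × (SD/difference)².

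- Speed: 45.7, so 46 (47 with the t distribution). The stated 47 reproduces.
- MFS: 73.2, so 74 (75 with the t distribution). The stated 62 does not reproduce. It would need an SD of about 1.75. This is a separate error, kept apart below.

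**Step 2: power of each endpoint at 62 per group.** The expected test statistic is difference / (SD × √(2/62)): 2.579 for MFS and 3.263 for speed. Power is Φ(statistic − 1.960).

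- MFS: 73.2% (72.5% with noncentral t).
- Speed: 90.4% (89.9% with noncentral t).

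**Step 3: either endpoint suffices.** Familywise error = 1 − P(both |Z| < 1.960) under the null. With independence this is 1 − 0.95² = 9.75%.

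| r | Familywise error |
|---|---|
| 0 | 9.75% |
| 0.3 | 9.5% |
| 0.5 | 9.1% |
| 0.8 | 7.8% |

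**Step 4: both required.** Alpha is at most 5%. Joint power is the bivariate normal probability that both statistics pass.

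| r | t-based marginals (72.5%, 89.9%) | Normal marginals (73.2%, 90.4%) | MFS granted 80%, speed 90.4% |
|---|---|---|---|
| 0 | 65.2% | 66.1% | 72.3% |
| 0.3 | 67.2% | 68.0% | 74.0% |
| 0.5 | 68.7% | 69.5% | 75.4% |

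At r = 0 these are simple products, for example 0.725 × 0.899 = 0.652. The last column removes the MFS sample-size error and isolates what the missing joint calculation costs: about 5 to 8 points below 80%. For 80% joint power on the protocol's inputs, about 78 to 80 per group are needed (r = 0.5 to 0), before any dropout.

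**Step 5: Holm at familywise 5%.** The smaller p-value is tested at 2.5% and, if it passes, the larger at 5%. Simulation with 2 million draws at 62 per group (normal approximation, r = 0 to 0.5) gives about 71–72% for MFS and 87–88% for speed. With t-based marginals the results are up to about 1 point lower. Holm thus costs about 2 points for MFS and 2 to 3 for speed against testing each at 5%.

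**The case against.** **A success rule can be left to the analysis plan, which is not shown.** This stands for the rule itself; its absence from a condensed article would not be a finding. It does not rescue the sample size, which the article fixes from two stand-alone 5%/80% calculations that were not made for either rule.

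**"Co-primary" and the single two-limb objective suggest that both are required.** That is a fair reading. If it is right, the inflated error rate disappears and only the power shortfall remains. The two consequences are alternatives and cannot both apply.

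**Much of the 65–70% comes from the MFS sample-size error.** Correct: MFS alone already has only about 73%. That is why 72–75% is shown beside it.

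**The power is not that of the planned analysis.** This is the strongest objection, and it stands. The article compares M6–M18 changes by mixed models, while the calculation uses the stated SD as the outcome SD. For change scores the two agree only at an M6–M18 correlation of 0.5, because the SD is multiplied by √(2(1 − ρ)). At 0.6 (multiplier 0.894) joint power is 78–80%, and at 0.7 (0.775) about 90%. With adjustment for the M6 value at ρ = 0.5 (multiplier √(1 − ρ²) = 0.866) it is 81–82%. At 0.4, change scores without adjustment do worse (multiplier 1.095, joint power 54–59%). The article gives no correlation, so it cannot claim the gain, but the shortfall is conditional on this assumption.

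**Stronger readings that the documents do not support.** A reader might infer that success could be claimed from any one of four tests (two endpoints, two analysis sets). The article says no such thing: it lists the two sets without ranking them, and their results would overlap heavily. A reader might also infer that the per-protocol comparison is biased because only GSC patients can fail the protocol. No per-protocol set is defined, the diary filling rate is not tied to one, and recurrent stroke ends participation in both arms. Any size put on such a bias would rest on invented inputs.

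**Conclusion.** The point holds for the sizing of the two co-primary endpoints. If either suffices, the familywise error is about 9–10% for r from 0.5 to 0. If both are required, alpha holds at 5% and joint power at 62 per group is about 65–70% on the protocol's own means and SDs, or 72–75% if 80% is granted for MFS.

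The error-rate figure depends only on the assumed correlation between endpoints. The power figures also depend on taking the stated SDs as outcome SDs, and a well-adjusted analysis could reach or pass 80%. What can be said firmly is that the stated 5% and 80% are properties of each endpoint taken alone, and that the article shows no basis for them as properties of the trial. The unranked analysis sets are a smaller matter of wording.

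**What to change.** - **State the success rule** before unblinded results are seen. One option is Holm at a two-sided familywise 5% with one claim per limb, which suits endpoints on different limbs. The other is to require both, each tested at 5%.
- **Restate power under that rule** in place of 80%. On the present inputs at 62 per group, Holm gives about 71% for MFS and 87–88% for speed; requiring both gives about 65–70% jointly. If the planned mixed model is expected to do better, give the assumed M6–M18 correlation and the power that follows.
- **Correct the MFS calculation** separately, since it feeds into every figure above.
- **Name intention to treat at M18 as the confirmatory analysis** and label per-protocol as supportive.

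The rule and the labels cost only wording. Holm costs about 2 to 3 points of power per endpoint and no patients, but wording alone does not restore 80%. If both are required and 80% joint power is wanted on the present inputs, about 78 to 80 per group would be needed before dropout. Otherwise the lower power should be stated openly.

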### Setting and recruitment

This multicenter trial involves six French centers (the medical centers in Saint-Etienne, Reims, Bordeaux, Toulouse, and Henri Mondor and Lariboisière university hospitals in Paris). Each of these centers admits > 100 cases/year of patients with moderate to severe stroke-induced hemiparesis for specialized rehabilitation and will recruit 20 to 24 patients. A 3-year time-frame is planned for the study, each center starting the study once the total expected number of participants to be enrolled are lined up. The objective is thus to run the protocol simultaneously for all participants of each center, to make optimal use of the study therapist’s time (GSC group).

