### Procedures

In practice, each center uses two investigators in addition to the physical therapist for the GSC group. One is a clinical assessor (physician or physiotherapist) who remains blinded to the participant group; the other is the coordinator whose role is to organize the five semi-annual evaluations at D1, M6, M12, M18, M24. The coordinator will be unblinded and will be in contact with the participant’s physicians and with the physiotherapist involved in the GSC for the study center (for those participants in the GSC group). The coordinating investigator, after receiving the result of the randomization at the M6 visit, will:inform the participant and the physiotherapist who will apply the GSC method, for those participants randomized in the GSC group,notify the participant to continue with the usual therapy without further details, for those participants randomized in the CONV group.

Pre-inclusions will take place during a regular clinic visit. Participants meeting the selection criteria will be invited to participate in the protocol. A written descriptive documentation will be provided to them and potential study subjects will have at least 2 weeks to decide about participation. The informed consent will be signed and collected on the Day 1 visit of the study.

Phase 1 will then be a 6-month prospective follow-up period - with visits at D1 and M6 (Month 6) - to evaluate any changes under conventional community-based therapy. The same blinded investigator will evaluate participants at all follow-up visits, D1, M6, M12, M18, M24 (Table 1). At each visit, specific attention will be paid to any signs suggesting recurrent strokes with, if necessary, additional prescription of brain imaging. Should there be a diagnosis of recurrent stroke since study enrolment (calling for neuroradiologist opinion if needed), study participation will be discontinued and an Adverse Events form and Study Termination form will be filled out.

**Table 1 Tab1:** Template of recommended content for the schedule of enrolment, interventions, and assessments

	D1	M6	M12	M18	M24
Verification of inclusion and non-inclusion criteria	x				
Signature of written consent	x				
Full neurologic assessment	x				
Randomization		x			
Inventory of concomitant, local and systemic medical treatment s	x	x	x	x	x
Inventory of technical aids	x	x	x	x	x
Inventory of patient suppor t (caregivers, equipment)	x	x	x	x	x
Comfortable and maximal ambulation speed over 10 m s	x	x	x	x	x

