#### Descriptive analysis of the first phase

For Phase 1 (Day 1 to M6), descriptive analysis will explore:participant characteristics: age, sex, etiology of stroke, presence of significant sensory deficit, apraxia, neglect at Day 1 and M6.changes in function over the first 6 months of follow-up: ambulation speed, upper limb function (MFS) and secondary criteria.the current conventional therapy treatment: frequency of sessions with the community-based physiotherapist, number of visits and costs. The sum of the monthly frequency during the first 6 months of rehabilitation and the monthly cost of these sessions will be estimated for all 124 participants together. Comparisons will then be made between different levels of severity at onset and different age groups.

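### The 124 patients included at D1 equal the 2 × 62 required after randomisation at M6, so 62 per group is reached only if nobody leaves in those six months

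*Protocol article*

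**What the plan says.** All of this is in the protocol article.

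- **Sample size.** For MFS, 62 "subjects per group are required for a total of 124 participants". Walking speed needs at least 47 per group. The section ends: "A total of 124 patients will thus be included in the protocol". The number required and the number included are identical.
- **Procedures and Table 1.** Criteria are verified and consent is signed at D1. Randomisation is at M6, after an observational phase on conventional therapy.
- **Procedures, on events during follow-up.** "Should there be a diagnosis of recurrent stroke since study enrolment (calling for neuroradiologist opinion if needed), study participation will be discontinued". The rule runs from enrolment, so it acts before randomisation as well as after.
- **Descriptive analysis of the first phase.** For the D1 to M6 period, "the monthly cost of these sessions will be estimated for all 124 participants together".
- **Setting and recruitment.** Six centres recruit 20 to 24 patients each, "each center starting the study once the total expected number of participants to be enrolled are lined up", and all participants of a centre then run through the protocol at the same time.
- **Statistical analysis.** The main analysis concerns the randomised phase, M6 to M18.

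**The concern.** One number is assigned to two populations that stand six months apart: those who enter at D1 and those compared from M6. The two can be equal only if no participant is lost in between, and the article itself provides a reason for removal in that window. Withdrawal and death would add to it.

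At stake is the power claim for MFS, the co-primary outcome that sets the total. If 124 is the D1 count, the 62 per group on which the claim rests is a best case and not an expected value. The loss arises before randomisation, so it causes no bias between groups; the cost is precision.

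**Working it through.** **Inputs (Sample size section).** MFS mean 4.4, SD 1.9; improvement 30% versus 10%; two-sided alpha 5%, power 80%. Difference: (0.30 − 0.10) × 4.4 = 0.88; standardised, d = 0.88/1.9 = 0.463. Walking speed 0.63 m/s, SD 0.43; improvement 50% versus 10%. Difference: 0.40 × 0.63 = 0.252; d = 0.252/0.43 = 0.586.

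**Reproducing the plan's figures.** n per group = 2 × (1.96 + 0.8416)² / d².

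- Walking speed: 45.7, so 46; with the t distribution 46.7, so 47. The stated 47 reproduces.
- MFS: 73.2, so 74; with the t distribution 74.2, so 75. The stated 62 does not reproduce, and at 62 the t-test power is 72.5%. This is a separate matter. To keep it apart from loss before M6, power is shown on two bases: the plan's d = 0.463, and d = 0.507, the value at which 62 per group gives exactly 80%.

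**Number randomised.** With 124 at D1 and a proportion L lost before M6, n per group = 124 × (1 − L)/2. The documents give no L; 5%, 10% and 20% are assumptions.

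- L = 5%: 124 × 0.95/2 = 58.9, about 59
- L = 10%: 124 × 0.90/2 = 55.8, about 56
- L = 20%: 124 × 0.80/2 = 49.6, about 50

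**Power.** Two-sample t-test, two-sided 5%, 2n − 2 degrees of freedom, non-centrality d × √(n/2). For example, at n = 62 and d = 0.463 the non-centrality is 0.463 × √31 = 2.58.

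| Assumed loss D1 to M6 | n per group | MFS, if 62 gives 80% (d = 0.507) | MFS, plan's inputs (d = 0.463) | Walking speed (d = 0.586) |
|---|---|---|---|---|
| 0% | 62 | 80.0% | 72.5% | 89.9% |
| 5% | 59 | 78.0% | 70.4% | 88.4% |
| 10% | 56 | 75.8% | 68.1% | 86.7% |
| 20% | 50 | 70.9% | 63.0% | 82.7% |

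**How plausible is zero loss?** If each participant independently had a 2% chance of leaving before M6, the chance of keeping all 124 would be 0.98^124, about 8%. At 5% it would be 0.95^124, about 0.2%. These rates are illustrations.

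**Centre range.** 6 × 20 = 120 and 6 × 24 = 144. The range contains 124 and extends above it: 144 at D1 would still leave 124 after a loss of 1 − 124/144 = 13.9%. The Sample size section, however, fixes 124, and the first-phase description uses the same figure.

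**The case against.** The strongest reply is that this is an omission. A condensed article commonly leaves the loss allowance and any replacement rule to the full protocol, which is not shown. That stands for the missing allowance taken alone. It does not cover what the article does state: a required number and an included number that are equal, with randomisation six months after inclusion.

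A second reply is that 124 might mean those who reach M6. The Research design section speaks of a randomised study on 124 participants, and the first-phase cost sum could be read as covering patients who completed that phase. The reading is possible, but the word used for 124 is inclusion, which the article places at D1. At the least, the two counts are not separated.

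A reader might also infer more than the text supports:

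- *That 62 per group cannot be reached.* It is reached if nobody leaves before M6, or if centres recruit towards the top of their range.
- *That lost patients are not replaced.* No section excludes replacement. The batch start makes it awkward, no more.
- *That 6 × 20 = 120 is itself a shortfall.* Nothing says that every centre will recruit its minimum.
- *That loss explains the whole gap from 80% to 68%.* With the plan's inputs, the fall from 80% to 72.5% comes from the MFS calculation. A 5% loss accounts for about 2 points and a 10% loss for 4 to 5.

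Finally, the table uses an unadjusted t-test, whereas mixed models on changes from M6 are planned. An analysis adjusted for baseline with a correlation of about 0.39 would make 62 sufficient under the plan's inputs. That shifts the starting level of power; fewer patients randomised would still lower it.

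**Conclusion.** The point holds in a limited form. As written, 124 is both the number included at D1 and the exact number required for the randomised comparison, so the stated group size and MFS power assume no loss over six months, although the article provides for removal in that period.

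The size depends on an assumed loss rate: about 2 points of MFS power at 5%, 4 to 5 at 10% and 9 to 10 at 20%, on either basis. Walking speed is not at risk, since 50 per group exceeds the 47 it needs. Losses between M6 and M18 are not counted here. This is a moderate weakness in the planning of one co-primary outcome and does not threaten the validity of the comparison.

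**What to change.** In the Sample size section, state whether 124 is the number included at D1 or the number randomised at M6. Then bring the Setting and recruitment section (20 to 24 per centre) and the first-phase description (all 124 together) into line with that choice.

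If 124 is the D1 count, add the expected loss before M6, the expected number randomised per group and the MFS power at that number. If it is the number randomised, say so and let the D1 count and the first-phase denominator differ from it.

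The cost is a sentence and a restated figure; the downside is a slightly less favourable stated power.

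Recruiting towards 144 is not proposed as the remedy. Any surplus that reached M6 would be randomised, and half of it would need home sessions every 15 days for a year from therapists whose time already shapes the design. Under the plan's own MFS inputs, 62 randomised per group would still give only 72.5% power.
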